#### Secondary Outcomes

Secondary outcomes are listed and elaborated as follows:

1) Rate of ECMO weaning will be calculated according to date of ECMO weaning fulfilled.2) Total length of ready for ECMO weaning refers to exact length in day till patients fulfill all the criteria of ready for ECMO weaning according to daily checkout records (14).3) Total length of ECMO weaning refers to exact length in day for patients treated with ECMO therapy (29).4) Rate of mechanical ventilation weaning will be calculated according to date of mechanical ventilation weaning fulfilled. Daily screening of mechanical ventilation weaning will be strictly performed with checklist shown in Table 7 according to the American Thoracic Society and the American College of Chest Physicians Clinical Practice Guideline (30).5) Total length of mechanical ventilation refers to exact length in day for patients treated with mechanical ventilation.6) All-cause mortality is defined as rate of death due to any causes and will be calculated according to date of death (31).7) Rate of major post-ECMO complications refers to rate of complications occurred after ECMO including but not limited to ECMO-related complications (e.g., thromboembolism), mechanical ventilation-related complications (e.g., pneumonia), newly developed myocardial infarction, acute kidney injury, neurologic events (e.g., stroke, seizures), and multiple organ failure (32). Information of major post-ECMO complications will be collected in the Complication Recording Sheet (Table 8).8) Diaphragmatic thickness and mobility refer to ultrasound-guided evaluation of diaphragmatic thickness and mobility under M-mode (33).9) Extracorporeal membrane oxygenation unit LOS accounts for length in day for stay of patients in the ICU unit.10) Total hospital LOS accounts for total hospital LOS in day for stay of patients in both the ECMO unit and other departments.11) Total cost for hospitalization will be calculated by addition of the cost of all the units and department admission.12) Cerebral performance category will be recorded, for those successfully weaning of ECMO, to reflect post-ECMO neurological status (34).13) Activities of daily living will be evaluated, for those successfully weaning of ECMO, with Katz Index (35).14) Health-related quality of life will be measured, for those successfully weaning of ECMO, with SF-12 (36).

**Table 7 T7:** Mechanical ventilation weaning checklist.

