**Cardiovascular complications** **□ No □ Yes (If yes, then fill the following items)**
Date and time: ___ / ___ / ___, ___: ___
□ Cardiac arrest □ Newly developed myocardial infarction □ Heart failure □ Myocardium stunning (Ultrasound) □ Newly developed hypertension requiring vasodilator therapy □ Shock (□ Cardiogenic □ Hypovolemic □ Obstructive □ Distributive) □ North-south syndrome □ Tamponade (□ Blood □ Plasma □ Air)

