**Other complications** **□ No □ Yes (If yes, then fill the following items)**
Date and time: ___ / ___ / ___, ___: ___
Extremities complications: □ Distal ischemia □ Necrosis □ Deep venous thrombosis □ Osteofascial compartment syndrome □ Limb amputation Infection: Infection pathogen: □ G^+^ bacteria □ G^−^ bacteria □ Mycobacteria □ Fungus □ Virus and prion □ Protozoon Infection site: □ Blood □ Bone marrow □ Cerebrospinal fluid □ Ascites □ Hydrothorax □ Respiratory tract □ Skin, muscle, soft tissue □ Feces □ Urine □ Surgical site □ Wound site □ Other______ Bleeding: □ Cerebral hemorrhage □ Gastrointestinal bleeding □ Respiratory tract bleeding □ Cannulation site bleeding □ Thrombocytopenia □ Surgical site bleeding □ Hemolysis □ DIC □ Other______ Thrombosis: □ Pulmonary thromboembolism □ ECMO catheter thrombosis □ Limb thrombosis □ Mesenteric thrombosis □ Other______

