**ECMO-related complications** **□ No □ Yes (If yes, then fill the following items)**
Date and time: ___ / ___ / ___, ___: ___
□ Oxygenator failure □ Raceway rupture □ Crack in connectors □ Heat exchanger malfunction □ Cannula problems □ Clots or thrombosis of circuit component □ Pump failure □ Clots hemofilter □ Circuit change □ Other______

*ID, identified number; DIC, disseminated intravascular coagulation; ECMO, extracorporeal membrane oxygenation*.

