### Statistical Methods

The demographic and clinical characteristics collected at randomization will be presented as means with SDs or medians with interquartile ranges for continuous variables and as percentages for categorical variables, as appropriate.

For all the outcomes, we will estimate differences in effect size between the groups on both the intention-to-treat (ITT) and per protocol (PP) basis (39). Categorical variables will be compared with the chi-square or Fisher's exact tests and continuous variables will be compared with the Student's *t*-test or the Wilcoxon signed-rank test, as appropriate. The time effect of day the time-to-event outcomes identified (e.g., rate of ready for ECMO weaning, rate of ECMO weaning, rate of mechanical ventilation weaning, all-cause mortality, and rate of major post-ECMO complications) between the groups will be estimated with the Cox proportional hazards regression analysis and graphically illustrated using the Kaplan–Meier methods until CaRe-ECMO days 7, 14, 30, and 90, respectively (40). Variables, including total length of ready for ECMO weaning, total length of ECMO weaning, total length of mechanical ventilation, ECMO unit LOS, and total hospital LOS, will be treated with time-to-event data and will be analyzed with mixed-effects ordered logistic regression (41). Secondary outcomes with normal and non-normal distributions, including CPC, ADL, HRQoL, and diaphragmatic thickness and mobility, will be estimated for group differences with mixed-effects linear regression (41).

Considering that part of patients will definitely not reach the primary endpoint, i.e., ready for ECMO weaning at CaRe-ECMO day 7 for sensitivity purpose, we will assess the heterogeneity of the treatment effect on primary outcome and secondary outcomes in pre-specified subgroups of interest as per baseline data to be collected at randomization (e.g., age, gender, main diagnosis, comorbidities, the APACHE II score, ECMO mode, length since mechanical ventilation) by using exploratory *post-hoc* sensitivity adjusted analyses for any corresponding statistical methods mentioned above.

Interim analysis will be scheduled halfway through enrollment to check that there are no serious issues with respect to sample handling or data collection.

All the analyses will be conducted at a two-sided alpha level of 5% and will be performed using the Stata version 16 (StataCorp, College Station, Texas, USA) or other software, as appropriate.

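### The 'major' complications outcome has no severity rule or closed list and does not match its recording sheet, so a harm confined to one component would be diluted

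*Protocol article*

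**What the plan says.** Secondary Outcomes, item 7, defines the rate of major post-ECMO complications as the "rate of complications occurred after ECMO including but not limited to ECMO-related complications". It then gives examples: thromboembolism, ventilation-related complications such as pneumonia, and "newly developed myocardial infarction, acute kidney injury, neurologic events (e.g., stroke, seizures), and multiple organ failure". No grade, treatment threshold or closed list is stated. On the data source it says "Information of major post-ECMO complications will be collected in the Complication Recording Sheet (Table 8".

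Table 8 is a tick-box sheet with a date and time for each of five categories. Cardiac arrest, tamponade, cerebral hemorrhage and limb amputation appear there. So do circuit items ("Clots hemofilter □ Circuit change □ Other") and items such as "Cannulation site bleeding □ Thrombocytopenia", with no cut-off. One box does carry a treatment threshold: "Newly developed hypertension requiring vasodilator therapy". The sheet has no severity field.

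Statistical Methods puts the outcome among the time-to-event outcomes: "rate of major post-ECMO complications) between the groups will be estimated with the Cox proportional hazards regression analysis", to days 7, 14, 30 and 90. No complication rate, target difference or power for complications is given anywhere in the article.

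**The concern.** The name of the outcome promises a severity limit that the definition does not supply. Nothing says which ticks on Table 8 count as major. Taken literally, a hemofilter clot and a cardiac arrest are both events.

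The sheet and the definition also disagree. Two serious events named in item 7 have no box, and neither do the fractures that the withdrawal criteria give as examples of rehabilitation harm.

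Apart from all-cause mortality, this is the listed outcome that most directly compares harm between arms. The programme repositions cannulated patients, moves their joints and stimulates them electrically. The harms one would look for are specific: cannula problems, cannulation-site bleeding, pneumothorax, distal ischemia, thromboembolism, fracture. If these are pooled with many unrelated events, a real increase in one of them can disappear, and a null result would be reported as no difference in major complications.

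**Working it through.** **1. Definition against sheet.**

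| Event | Named in | Box in Table 8 |
|---|---|---|
| New myocardial infarction | Item 7 | Yes |
| Stroke, seizures | Item 7 | Yes (cerebral hemorrhage appears twice, under neurological and under bleeding) |
| Pneumonia | Item 7 | Yes (pulmonary infection) |
| Thromboembolism | Item 7 | Yes (several boxes) |
| Acute kidney injury | Item 7 | No |
| Multiple organ failure | Item 7 | No |
| Rib fracture, limb fracture | Withdrawal criteria | No |

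The free 'Other' lines sit under infection site, bleeding, thrombosis and ECMO-related complications. None is a natural place for the missing events.

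**2. Number of boxes.** Counting infection once and ignoring the subtypes of shock and tamponade: 3 neurological + 8 cardiovascular + 5 respiratory + 5 extremity + 1 infection + 9 bleeding + 5 thrombosis + 10 ECMO-related = 46.

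**3. Is the outcome near ceiling?** The article gives no rates. If every box had the same probability p and the boxes were independent, the chance of at least one would be 1 − (1 − p)^46. This is 37% at p = 1%, 61% at 2% and 91% at 5%. The boxes clearly overlap, and positive correlation lowers these figures. A ceiling is possible but not shown.

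**4. Dilution of a single-component harm.** There is no figure in the article to reproduce for this outcome. Inputs taken from it: 183 per arm and two-sided alpha of 5%. Assumptions: one harm rises from 5% to 15%; all other complications together have background probability b, equal in both arms and independent of that harm; hazards are constant.

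- Composite probabilities: P0 = 1 − (1 − b)(0.95) and P1 = 1 − (1 − b)(0.85).
- Hazard ratio: HR = ln(1 − P1) / ln(1 − P0).
- Expected events: D = 183 × (P0 + P1).
- Cox power: Φ(√(D/4) × ln HR − 1.96), plus the small opposite tail. Binary power: two-proportion normal approximation with pooled variance under the null.

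| Background b | P0 | P1 | HR | Events | Power, binary | Power, Cox |
|---|---|---|---|---|---|---|
| Harm tested alone | 5% | 15% | – | – | 89% | – |
| 20% | 24.0% | 32.0% | 1.41 | 102 | 40% | 41% |
| 30% | 33.5% | 40.5% | 1.27 | 135 | 28% | 29% |
| 60% | 62.0% | 66.0% | 1.12 | 234 | 13% | 13% |
| 90% | 90.5% | 91.5% | 1.05 | 333 | 6% | 7% |

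More than half the power is lost at a 20% background, far from any ceiling.

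**5. A harm that raises complications overall.** The detectable HR at 80% power is exp[(1.96 + 0.84) / √(D/4)]. With 30% of 366 patients having an event, D = 110 and the HR is 1.71. With 90%, D = 329 and the HR is 1.36. For this kind of harm a high event share helps the Cox analysis.

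**The case against.** A reader might infer that nearly every patient will have the outcome. The documents do not support that: it needs rates they do not give, and independence that overlapping boxes contradict.

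A reader might also infer that the comparison cannot show a harm of rehabilitation. That is too absolute, because step 5 shows that Cox regression keeps power against a rise in the overall complication hazard.

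Further points on the other side are fair:

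- The article says that information is collected in Table 8. It does not say that every tick is a major event or that only the first tick is analysed. Categories are dated separately, so component comparisons remain possible.
- A condensed article may leave grading to a fuller document, and item 7 cites a source that is not shown.
- The daily monitoring sheet (Table 11) records creatinine and renal replacement therapy, so acute kidney injury might be reconstructed.
- Safety has other routes: periodic review, recorded reasons for stopping sessions, and withdrawal for rehabilitation-related events.
- Reducing some listed complications, such as atelectasis and thrombosis, is an aim of the programme, so the outcome is not purely a safety measure.

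These points limit the claim but do not remove it. The article does state a definition, a sheet and an analysis, and those are open-ended and inconsistent with each other. The text does not say that the cited source supplies a severity rule. No component comparison is named. Recorded reasons for stopping sessions do not give a between-arm comparison of these harms.

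**Conclusion.** The point holds in a limited form. 'Major' has no severity rule, the list is open, and the sheet lacks boxes for two events in the definition and for the rehabilitation harms named elsewhere in the article. As written, the outcome is any complication. A harm confined to one component then loses much of its detectability: from 89% power alone to about 40% at a 20% background, 13% at 60% and 6–7% at 90%. These figures rest on an assumed 5% versus 15% harm, an assumed background equal in both arms, independence and constant hazards. Only the 183 per arm and the alpha level come from the article.

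It is not established that the outcome sits at a ceiling, or that the comparison is blind to every harm. The practical consequence is that a statement of no difference in major complications would be weak reassurance about the specific harms that matter for this intervention.

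**What to change.** 1. In item 7, delete the open-ended phrase. Before unblinding, fix a closed list of serious events that covers those item 7 names and the grave events already on Table 8, for example cardiac arrest, cerebral hemorrhage, tamponade and limb amputation. State which box or boxes define each event, and count cerebral hemorrhage once.
2. Add boxes to Table 8 for acute kidney injury, multiple organ failure and fracture.
3. Report all remaining boxes as counts by arm, outside the composite.
4. Add one pre-named safety table by arm, with risk differences and 95% confidence intervals, for cannula problems, cannulation-site bleeding, pneumothorax, distal ischemia, thromboembolism and fracture.

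The cost is a small change to the form, revised wording in item 7 and one extra table. The composite will have fewer events, so its interval will be wider. No treatment or visit changes.

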**Contraindications for VA-ECMO**
1. Irreversible non-cardiac organ failure limiting survival (e.g., severe anoxic brain injury or metastatic cancer)
2. Irreversible and incapacitating central nervous system pathology
3. Irreversible and incapacitating cardiovascular system pathology
4. Systemic bleeding
5. Aortic dissection
6. Limited vascular access (severe peripheral arterial disease, extreme obesity, amputated limbs, among others)
7. Older age (increasing risk of death with increasing age)

*VA-ECMO, venoarterial extracorporeal membrane oxygenation; LVEF, left ventricular ejection fraction; SvO_2_, mixed venous oxygen saturation; ROSC, return of spontaneous circulation; VAD, ventricular assist device*.

* *Vasoactive-inotrope score (VIS): (Epinephrine dose + Norepinephrine dose) μg/kg/min × 100 + (Dopamine dose + Dobutamine dose) μg/kg/min*.

Patients will be withdrawn from the trial if: (1) the guardian makes such a request with no reasons; (2) the patient develops adverse events due to cardiopulmonary rehabilitation (e.g., rib fracture, limb fracture); and (3) the patient develops ECMO-related complications (e.g., bleeding, thromboembolism, severe infection) and is ever unsuitable for participating in the trial according to the point of view by clinicians.

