### Interventions

#### CaRe-ECMO Group

Patients in the CaRe-ECMO group will be treated with usual care, ECMO therapy, and cardiopulmonary rehabilitation program. Usual care normally comprises pharmacotherapy, mechanical ventilation, continuous renal replacement therapy (CRRT), intra-aortic balloon pump (IABP), and specific nursing for ECMO therapy and their original injuries, as appropriate. In addition, patients will receive cardiopulmonary rehabilitation from a multidisciplinary team (e.g., clinicians, rehabilitation physicians, nurses, and therapists) who were fully trained to provide care to every ECMO-supported patient when medically appropriate. A core group of clinicians and therapists (e.g., XL, ZS, XC, YZ, YC, and SW) are competent in the use of a screening procedure (e.g., stability of hemodynamic and vital signs, stability of blood coagulation, stability of homeostasis, stability of mechanical ventilation, stability of ECMO flows, and stability of cannulation position and tightness) to determine appropriateness and safety for cardiopulmonary rehabilitation delivery according to the experience from the University of Maryland Medical Center (4). Detailed daily eligibility screening flowchart for cardiopulmonary rehabilitation is shown in Figure 2. Once the patients pass the screen, the therapists will proceed to provide protocolized cardiopulmonary rehabilitation program, which encompasses five evidence-based components according to literature review: (1) positioning; (2) passive range of motion (PROM) training; (3) neuromuscular electrical stimulation (NMES); (4) surface electrical phrenic nerve stimulation (SEPNS); (5) respiratory proprioceptive neuromuscular facilitation (PNF) techniques; and (6) airway clearance techniques (22–24). Detailed content and protocol are given in Table 4. It should be emphasized that hemodynamic and vital signs, ECMO flows, and cannulation position and tightness will be continuously monitored during each rehabilitation session. In case any adverse events occur, cardiopulmonary rehabilitation session will be discontinued. Corresponding reasons for discontinuous and exact length of therapy will be recorded.

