**Neurological complications** **□ No □ Yes (If yes, then fill the following items)**
Date and time: ___ / ___ / ___, ___: ___
□ Cerebral hemorrhage □ Cerebral infarction □ Epileptic seizure

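### The Complication Recording Sheet (Table 8) has no field for acute kidney injury or multiple organ failure, although both are named components of the complication outcome it is meant to record

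*Protocol article*

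**What the plan says.** Secondary Outcomes, item 7, defines the rate of major post-ECMO complications by an open list. It names ECMO-related events such as thromboembolism and ventilation-related events such as pneumonia, and continues with "newly developed myocardial infarction, acute kidney injury, neurologic events (e.g., stroke, seizures), and multiple organ failure (32). Information of major post-ECMO complications will" be collected on a named form. That last sentence in full fixes the instrument: "Information of major post-ECMO complications will be collected in the Complication Recording Sheet (Table 8").

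Table 8 is printed as a complete form with five blocks, each with its own date and time line:

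- Neurological: "Cerebral hemorrhage □ Cerebral infarction □ Epileptic seizure".
- Cardiovascular: opens with "Cardiac arrest □ Newly developed myocardial infarction □ Heart failure □ Myocardium stunning (Ultrasound") and goes on to hypertension, shock, north-south syndrome and tamponade.
- Respiratory: five lung conditions.
- Other: "Extremities complications: □ Distal ischemia □ Necrosis □ Deep venous thrombosis □ Osteofascial compartment syndrome □ Limb amputation", followed by infection, bleeding and thrombosis.
- ECMO-related: faults of the circuit and device.

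The Data Collection section names a different source for the same rate, namely daily evaluations in the medical records. Statistical Methods lists the rate among the time-to-event outcomes, to be analysed by Cox regression and Kaplan–Meier curves to days 7, 14, 30 and 90.

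On harms of the programme, Eligibility and Withdrawal Criteria provides for withdrawal if "the patient develops adverse events due to cardiopulmonary rehabilitation (e.g., rib fracture, limb fracture"). For interrupted rehabilitation sessions, the CaRe-ECMO Group section says: "Corresponding reasons for discontinuous and exact length of therapy will be recorded".

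**The concern.** An outcome definition and the form that serves it should name the same events. Here the definition is wider than the form. A site that relies on the designated sheet has nowhere to enter two of the events that the protocol itself calls major complications.

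The analysis makes this matter. A Cox model needs an event indicator and a date for every patient. If kidney injury or organ failure is a patient's only major complication, the sheet shows that patient as event-free. If another complication follows, the sheet dates the first event too late, so the patient may be event-free at an early cut-off such as day 7 and an event only at a later one. The same form serves both arms, so the gap does not by itself favour either. It does lower the event count, and the hazard ratio then describes a narrower outcome than the one reported.

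Renal failure is plainly foreseen in this population: continuous renal replacement therapy (CRRT) is listed within usual care and appears as a daily item on Table 11.

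**Working it through.** No figure in the plan is at issue, so the check is a field-by-field comparison.

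**Step 1. Named components (item 7) against Table 8.**

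| Component named in item 7 | Field in Table 8 |
|---|---|
| ECMO-related, e.g. thromboembolism | Present: thrombosis items and ECMO-related block |
| Ventilation-related, e.g. pneumonia | Present: pulmonary infection, ventilator-associated lung injury |
| New myocardial infarction | Present: cardiovascular block |
| Neurologic, e.g. stroke, seizures | Present: hemorrhage, infarction, epileptic seizure |
| Acute kidney injury | None |
| Multiple organ failure | None |

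Result: 6 − 4 = 2 named components without a field.

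**Step 2. Could a free-text line take them?** Table 8 has four blanks for other events. Three belong to infection site, bleeding and thrombosis. The fourth closes the list of circuit and device faults. The neurological, cardiovascular and respiratory blocks have none, and there is no general line. The last blank could be used informally, but different staff would use it differently and the counts would not be consistent.

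**Step 3. Are there other sources?**

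- Data Collection refers to the medical records, without saying how an event is identified in them.
- Table 11 holds daily creatinine, fluid output and CRRT, and items for other organs such as bilirubin, platelets, Glasgow Coma Scale, mean arterial pressure and vasoactive dose.

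These are raw values. The article gives no rule that turns them into a dated kidney injury or a dated multiple organ failure. They permit reconstruction, but they do not constitute an event record.

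**Step 4. Named rehabilitation harms.** Neither rib fracture nor limb fracture has a box in Table 8. This is a lesser observation, because item 7 does not list fractures and nothing in the article assigns them to Table 8.

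**The case against.** The strongest reply is that Table 8 is not the only source. Data Collection says the rate comes from daily evaluations in the medical records, Table 11 records organ function every day, and Data Management and Monitoring refers to standardized eCRFs that are not shown. A reader might infer from Table 8 alone that the reported rate will simply omit kidney injury and organ failure. The documents do not support that: a site following the whole plan has a route to both. What remains is that item 7 designates Table 8 in so many words, that the other route has no stated event definition, and that the two sections disagree on the source.

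A reader might also infer that fractures caused by rehabilitation will never enter a between-arm comparison. That goes too far. The withdrawal criteria give fractures as examples only, safety and withdrawals are reviewed periodically, and a separate adverse-event form may well sit in the full protocol. The most that can be said is that the article states no route for them into such a comparison.

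Cerebral hemorrhage appears in both the neurological block and the bleeding list, which may suggest double counting. In a time-to-first-event analysis a second tick for the same hemorrhage changes neither whether nor when the patient had an event, and the article plans no tally by category.

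Finally, this is one of fourteen secondary outcomes, and the primary outcome is untouched. That stands, and it limits the weight of the point.

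**Conclusion.** The mismatch is real. Two of the six kinds of event named in item 7 cannot be counted or dated from the form designated for them. Table 8 is printed in full, so neither condensation into an article nor text extraction explains the gap.

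The conclusion concerns the sheet, not everything the trial may collect. It rests on Table 8 being used as printed. How many events would be lost cannot be stated: the documents give no incidence of either event, no proportion of patients in whom it would be the only major complication, and no indication of how much the medical records would recover. Any number of patients attached to this point would be an assumption. The correction is nonetheless worth making, because it is specific and cheap, and it makes a stated outcome obtainable from its stated source.

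**What to change.** Table 1 gives recruitment as not yet started, so the form can be changed before the first patient:

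1. Add acute kidney injury and multiple organ failure to Table 8, each with its own date and time, a stated definition, and completion in both arms. Since CRRT is part of usual care, the definition should say how a condition already present at randomization is handled.
2. Cross-check recorded kidney injury against the creatinine and CRRT items of Table 11.
3. Reconcile Secondary Outcomes item 7 with Data Collection, so that one source is primary and the role of the other is clear.
4. As a minor addition, put a dated tick box for rib or limb fracture on the sheet for both arms. This gives the harms named in the withdrawal criteria a stated route into a between-arm comparison. The log of interrupted sessions cannot do this, because the control arm has no rehabilitation sessions during the randomized phase.

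The cost is a few tick boxes and two definitions. The reported complication rate may be higher, because more of what the protocol defines as a complication will be recorded.
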